### Step 4: Producing program components and materials

Taking the end products of the previous steps into account, we decided to develop one intervention containing three web-based sessions containing tailored pieces of advice addressing mostly personal and psychological determinants. A program plan including the scope, sequence and program materials was developed [44], which is described below. During the process of producing program components and materials, intended program participants and the Linkage group were consulted to determine the preferences for program design by conducting focus group interviews and short voting sessions.

#### **
*Scope and sequence*
**

Based on brainstorms and voting sessions with members of the target group, we named the intervention *Online Pestkoppenstoppen* with three web-based tailored pieces of advices named: (1) *Think strong, feel better*; (2) *Stop the bully now!*; and (3) *You are doing great, can you do better?*. Each advice is preceded by several questionnaires – measuring tailoring and effect variables - that take approximately half an hour to complete, and each advice takes approximately 45 minutes to complete. The pieces of advice are offered divided over three months, and e-mails and text messages are used to remind the participant of participation (see Figure 5). The intervention can be found and is accessed on http://www.pestkoppenstoppen.nl.

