### Step 6: Planning for evaluation

The evaluation of the program - which is described below - was planned. The research on the effectiveness of the intervention *Online Pestkoppenstoppen* has been approved by the Medical Ethics Committee of the Atrium Hospital of Heerlen (NL39072.096.12; METC nr. 12-T-126), and is registered in the Dutch Trial Register (http://NTR3613).

#### **
*Design and procedure*
**

A three-group (experimental group, general information group and waiting list control group) randomized control trial (RCT) will be conducted to evaluate the efficacy of the intervention, with self-assessed measures at baseline (T0), before advice two (T1), before advice three (T2), a half-year post start (T3) and 1 year post start (T4) (see Figure 7). Statements about the effectiveness of the three tailored web-based pieces of advice compared to general information can be made by comparing the experimental group with the general information group. The waiting list control group allows for controlling internal validation issues such as aging. However, this group does not receive measurements at T4. After the research, both the waiting list control group and general information group will be allowed to use the intervention.

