To evaluate the effectiveness of the intervention, several concepts will be measured via self-reported questionnaires. The primary outcomes of this study are frequency of (cyber)bullying, psychological wellbeing, problem behavior, school performance and truancy. These will be assessed at baseline (T0), 6 (T3) and 12 months (T4) follow-up. The secondary outcomes of this study (i.e. moderators or working mechanisms (mediators) of the intervention) are irrational thoughts, self-efficacy, coping with cyberbullying and self-esteem. These will be assessed at baseline (T0), after 1 (T1), 2 (T2), 6 (T3) and 12 months (T4) follow-up. At baseline, several moderators will be measured as well (i.e. demographic characteristics such as gender, age, educational level). In addition, a process evaluation at T3 will be conducted to examine potential moderators.

#### **
*Power calculation*
**

The power analysis is based on two important dependencies: decrease in psychosocial problems and the amount of cyberbullying victims after the intervention. The outcomes are based on the PaS training [122]. A power calculation (effect size = .3; power = .80; intracluster correlation coefficient = .1) showed that at baseline about 446 participants were needed (based on a dropout rate of 20%). Based on previous studies we suspect that 25% of the adolescents between 12 and 15 years can be classified as cyberbullying victims, and that 50% of the adolescents are willing to participate. This results in 3570 adolescents, divided over 30 schools, with each school having 4 or 5 classes.

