## Discussion

The aim of this paper was to provide a detailed description of the systematic development of the three web-based tailored pieces of advice for cyberbully victims that aimed at increasing psychological wellbeing, and decreasing victimization, problem behavior, school problems and truancy. In this intervention, cyberbully victims learn how to recognize, dispute and replace irrational thoughts with rational thoughts. Furthermore, their ineffective coping strategies are replaced with effective coping strategies, and they learn how to use the Internet and mobile phone in a safe and secure manner. The intervention is delivered online, via digital guides in digital environments. Digital guides provide information, ask questions, and show videos, pictures, comics and animations.

This intervention has several strengths. First, in developing, implementing and evaluating a systematic approach [44], the Intervention Mapping approach is used. In the process of developing the intervention, empirical evidence, theories, guidelines and recommendations from the cyberbullying and bullying intervention and prevention literature were used to build a solid framework. Second, the intervention aims to change multiple determinants that were found in a study done by Jacobs et al., [70]. Third, guidelines and recommendations from other, not related to (cyber)bullying, intervention studies and theories were used, combined with results from focus groups interviews with the target groups. Fourth, this intervention is tailored to the specific needs of the target group: cyberbully victims are often unwilling to tell a teacher, parent or other adult that they need help. Therefore, they may feel more comfortable to [33] find help anonymously on the Internet [31]. Furthermore, we tried to incorporate all preferences of the target group as indicated in the pre-tests and pilot tests. Fifth, web-based computer tailored interventions can be used any time [35], can reach a lot of people in a relatively cheap way [36], and allow for tailoring [37], which has the potential for a successful health promotion technique [38,39]. Sixth, the planned RCT allows several important conclusions to be drawn. Finally, a process evaluation allows us to draw conclusions about several working mechanisms.

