This intervention has a number of limitations. First, it was difficult to reduce the number of questions in the questionnaires we used for evaluation purposes. In the focus group interviews, members of the target group clearly stated that too many questions will lead to drop-out, because answering many questions is experienced as boring and fatiguing. Furthermore, too many questions may cause no-saying or yes-saying and response fatigue (for a review, see [123]), leading to less reliable results. Second, the intervention may contain too much information. Based on the literature, it was decided to include the 5G-schema, coping strategies, social skills, planning and safety instructions. In focus group interviews, members of the target-group mentioned the large amount of information making it difficult to remember everything. Third, we cannot exactly check the degree of usage on the experimental and general information. This may hamper the interpretation of the results. Therefore, we have added process evaluation questions, in which we ask the participants if they have read the information.

In conclusion, the *Online Pestkoppenstoppen* program seems to be a promising start in solving current cyberbullying problems. The results of the evaluation studies, which will be reported in other papers, may contribute to the knowledge about how to stop online victimization and how to use tailoring and web-based interventions in this purpose. Additionally, this intervention may also affect offline victimization, because despite the differences, cyberbullying and traditional bullying also have some overlapping characteristics [24,25,27]. The results can be used as input for other web-based and computer-tailored interventions aimed at cyberbully victims. If the studies point out that the intervention is effective in its purpose, we have an intervention ready for implementation on a large scale.

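### The T3 process evaluation is planned as a source of moderators, but it is collected after randomisation and delivery, so effect differences across it would not be randomised comparisons

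*Protocol article*

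**What the plan says.** All references are to the protocol article.

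- **Process evaluation (Step 6, Measurement instruments).** "In addition, a process evaluation at T3 will be conducted to examine potential moderators".
- **Secondary variables (same section).** "The secondary outcomes of this study (i.e. moderators or working mechanisms (mediators) of the intervention) are irrational thoughts, self-efficacy, coping with cyberbullying and self-esteem". Their schedule follows: "These will be assessed at baseline (T0), after 1 (T1), 2 (T2), 6 (T3) and 12 months (T4) follow-up". The section also lists demographic moderators taken at baseline.
- **Primary outcomes (same section).** They are measured at T0, T3 and T4.
- **Timing.** Step 6, Design and procedure, places T3 half a year after the start. Step 4, Scope and sequence, says: "The pieces of advice are offered divided over three months". The third advice begins two months after the start.
- **Content of the process evaluation (Discussion, limitations).** The article concedes that use of the material cannot be tracked exactly, and continues: "we have added process evaluation questions, in which we ask the participants if they have read the information".
- **Purpose as given in the Discussion (strengths).** "a process evaluation allows us to draw conclusions about several working mechanisms".

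**The concern.** A moderator says for whom a treatment works, so it has to be fixed before treatment starts. Only then does randomisation, here of schools, make the arms comparable at each level of it. A variable collected at T3 does not meet that condition. Whether a pupil read the material depends on what the arm offered and on how motivated the pupil was, and motivation may also improve the outcome. Readers in the tailored arm and readers in the general-information arm have read different things and may be different kinds of pupil. The answer is also a self-report given when the outcome is measured, so outcome status could colour it.

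What is at stake is any later statement about the pupils for whom the programme works. The Background section sets that as a requirement for a sound intervention. A finding that the advice helps those who read it could arise with no true difference in effect.

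**Working it through.** The plan gives no figure on this point, so there is none to reproduce. The check has two parts: timing, and the size of the possible artefact.

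**1. Timing.** Delivery runs over three months and T3 falls at six. The process evaluation is therefore after randomisation, after delivery, and concurrent with a primary-outcome measurement.

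**2. Size.** The only input from the document is the effect size of 0.3 in the power calculation; reading it as a standardised mean difference is my assumption. Everything else below is assumed for illustration.

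Model: an unmeasured trait U (motivation, SD 1) has correlation g with the outcome Y (SD 1 within arm). Reading is recorded if aU + noise (SD 1) is above zero, so half the pupils read. The true effect is the same for everyone. The correlation of U with the reading tendency is a/√(1 + a²). Mean U among readers is that correlation × √(2/π) = correlation × 0.798, and minus that among non-readers.

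*Scenario A: true effect 0.30, link stronger in the intervention arm (a = 0.8 against 0.4).*
- Correlations: 0.8/√1.64 = 0.625 and 0.4/√1.16 = 0.371.
- Mean U among readers: 0.625 × 0.798 = 0.498 and 0.371 × 0.798 = 0.296; difference 0.202.
- Bias per stratum: g × 0.202 = 0.06 at g = 0.3 and 0.10 at g = 0.5, positive in readers and negative in non-readers.

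A simulation of 2,000,000 pupils without clustering agrees. It also covers cases where reading is more common in the intervention arm (a shift of 0.5 or 1 in the reading tendency):

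| g | Shift | Effect in readers | Effect in non-readers | Spurious difference |
|---|---|---|---|---|
| 0 | 0, 0.5 or 1 | 0.30 | 0.30 | 0.00 |
| 0.3 | 0 | 0.36 | 0.24 | 0.12 |
| 0.3 | 1 | 0.28 | 0.14 | 0.14 |
| 0.5 | 0 | 0.40 | 0.20 | 0.20 |
| 0.5 | 1 | 0.27 | 0.03 | 0.24 |

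Splitting the same data on the trait as it stood at baseline gives 0.30 in both strata in every row.

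*Scenario B, less favourable: true effect zero, motivation drives reading in one arm only, correlation 0.7 with the reading tendency, 50% readers in both arms.*
- Bias per stratum: 0.7 × 0.798 × g = 0.11 at g = 0.2 and 0.22 at g = 0.4, positive in readers and negative in non-readers.
- The gap between strata is twice that: 0.22 and 0.45.

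*Scenario C: the same link and the same reading rate in both arms.* Mean U among readers is equal in the two arms, so the bias is g × 0 = 0.

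**The case against.** The strongest reply is that the article states no moderation model. The sentence stands in a section on what is measured and when; how process data enter an analysis may be set out in a fuller document. The limitations paragraph gives the reading questions a milder role, as help in interpreting results when use cannot be tracked. This is largely fair. It means the bias could arise, not that it will. It does not remove the sentence, which names examining moderators as the purpose of a T3 measurement.

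The size also rests on assumed correlations and on selection that differs between arms. That stands too: Scenario C gives zero.

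A reader might infer more than the text supports:

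- *That the four secondary scales cannot be moderators.* All four are measured at T0, and their T0 values are legitimate moderators, as are the baseline demographics. Nothing says that later values will be used as moderators. The joint label leaves the roles unassigned, which is a matter for clarification.
- *That the waiting-list arm would be classified by reading.* The limitations paragraph speaks of the two arms that have material, and nothing says the waiting-list group answers these questions.
- *That Measurement instruments and the Discussion contradict each other.* One speaks of moderators and the other of working mechanisms, but a process evaluation can serve both. The difference in wording is a weak point.

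**Conclusion.** The point holds for the T3 process evaluation. As worded, the plan would look for moderators among variables that follow randomisation and delivery, and the one item described is self-reported reading. Effect differences across such a variable are not randomised comparisons. They could be spurious if motivation drives both reading and outcome and if selection into reading differs by arm.

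As an illustration, the strata differ falsely by about 0.12 to 0.24 SD when selection is merely stronger in one arm. When it occurs in one arm only, each stratum is biased by 0.11 to 0.22 SD in opposite directions. With equal selection, or a trait unrelated to outcome, the artefact is zero. None of the correlations comes from the document.

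It would be wrong to conclude that the trial's main result is at risk. The primary comparison between arms does not condition on reading and is unaffected; only explanatory analyses are touched.

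**What to change.** In Step 6, Measurement instruments:

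1. Restrict moderator analyses to T0 variables: the demographics and the T0 values of irrational thoughts, self-efficacy, coping and self-esteem.
2. Treat later values of those four scales as mediators only, measured before the outcome they explain, for example T1 and T2 values for outcomes at T3 and T4. Mediators are also post-randomisation, so such results need the usual caution about shared causes of mediator and outcome.
3. Replace the moderator purpose of the T3 process evaluation with descriptive reporting of use and reading in each arm that received material.

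I do not propose a complier-average estimate as a substitute. The main comparator has its own material to read, reading is self-reported, and allocation is by school, so its assumptions would be hard to defend here.

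The cost is wording; no new data are needed. The downside is that a subgroup claim of benefit among those who read the advice is no longer available.

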## Discussion

The aim of this paper was to provide a detailed description of the systematic development of the three web-based tailored pieces of advice for cyberbully victims that aimed at increasing psychological wellbeing, and decreasing victimization, problem behavior, school problems and truancy. In this intervention, cyberbully victims learn how to recognize, dispute and replace irrational thoughts with rational thoughts. Furthermore, their ineffective coping strategies are replaced with effective coping strategies, and they learn how to use the Internet and mobile phone in a safe and secure manner. The intervention is delivered online, via digital guides in digital environments. Digital guides provide information, ask questions, and show videos, pictures, comics and animations.

This intervention has several strengths. First, in developing, implementing and evaluating a systematic approach [44], the Intervention Mapping approach is used. In the process of developing the intervention, empirical evidence, theories, guidelines and recommendations from the cyberbullying and bullying intervention and prevention literature were used to build a solid framework. Second, the intervention aims to change multiple determinants that were found in a study done by Jacobs et al., [70]. Third, guidelines and recommendations from other, not related to (cyber)bullying, intervention studies and theories were used, combined with results from focus groups interviews with the target groups. Fourth, this intervention is tailored to the specific needs of the target group: cyberbully victims are often unwilling to tell a teacher, parent or other adult that they need help. Therefore, they may feel more comfortable to [33] find help anonymously on the Internet [31]. Furthermore, we tried to incorporate all preferences of the target group as indicated in the pre-tests and pilot tests. Fifth, web-based computer tailored interventions can be used any time [35], can reach a lot of people in a relatively cheap way [36], and allow for tailoring [37], which has the potential for a successful health promotion technique [38,39]. Sixth, the planned RCT allows several important conclusions to be drawn. Finally, a process evaluation allows us to draw conclusions about several working mechanisms.

This intervention has a number of limitations. First, it was difficult to reduce the number of questions in the questionnaires we used for evaluation purposes. In the focus group interviews, members of the target group clearly stated that too many questions will lead to drop-out, because answering many questions is experienced as boring and fatiguing. Furthermore, too many questions may cause no-saying or yes-saying and response fatigue (for a review, see [123]), leading to less reliable results. Second, the intervention may contain too much information. Based on the literature, it was decided to include the 5G-schema, coping strategies, social skills, planning and safety instructions. In focus group interviews, members of the target-group mentioned the large amount of information making it difficult to remember everything. Third, we cannot exactly check the degree of usage on the experimental and general information. This may hamper the interpretation of the results. Therefore, we have added process evaluation questions, in which we ask the participants if they have read the information.

In conclusion, the *Online Pestkoppenstoppen* program seems to be a promising start in solving current cyberbullying problems. The results of the evaluation studies, which will be reported in other papers, may contribute to the knowledge about how to stop online victimization and how to use tailoring and web-based interventions in this purpose. Additionally, this intervention may also affect offline victimization, because despite the differences, cyberbullying and traditional bullying also have some overlapping characteristics [24,25,27]. The results can be used as input for other web-based and computer-tailored interventions aimed at cyberbully victims. If the studies point out that the intervention is effective in its purpose, we have an intervention ready for implementation on a large scale.

## Abbreviations

IM: Intervention Mapping; POs: Performance objectives; PaS: Pleasure at school; RE(B)T: Rational Emotive (Behavioral) Therapy; APS: Active Problem Solving; COs: Change Objectives DT, Dynamic Tailoring; ST: Static Tailoring; RCT: Randomized Control Trial; YSR: Youth Self-Report.
